[figure not shown]

## **1. Project background and justification**

Diastasis of the rectus abdominis (DRA) consists of the separation of the belly of the two rectus abdominis (inter rectus distance) along the linea alba with fibrous division and widening of the same (1,2). The functions of the linea alba are diverse, on the one hand, to maintain the anterior rectus abdominis close together, to guarantee the stability of the spine, pelvis and pelvic floor and to intervene in the function of the abdominal muscles since it serves as an anterior anchorage for them (3 -5).

During pregnancy, ARD occurs physiologically due to hormonal elastic changes in the connective tissue and mechanical stresses on the abdominal wall produced by the growth of the fetus and the displacement of abdominal organs (6). It usually appears between the second and third trimester (6) and resolves spontaneously between 1 and 8 weeks after delivery (7,8). In some women, this spontaneous resolution does not occur after delivery, and it then becomes a pathologic condition that may persist for years after delivery (6,7).

In the scientific literature, the most studied exercise to check the behavior of the linea alba has been the abdominal crunch, finding in most cases a decrease in the inter-straight distance (IRD) compared to rest (9 -13). Mota et al. (12) and Chiarello et al. (9) show that, in women with children, this exercise causes a more accentuated decrease in IRD than in nulliparous women. Regarding transverse activation, an exercise recommended for the treatment of ARD (14,15), it causes an increase in DRI in most studies (10,12,16), which could be due to the orientation of its fibers that would help to tighten and widen the linea alba (1,12,17), favoring optimal functioning due to the tension created (13).

The abdominal hypopressive technique was described in 1980 by Marcel Caufriez, a Belgian physiotherapist (18). According to Caufriez, hypopressive exercises, initially intended for women in the postpartum period, produce a drop in abdominal pressure through diaphragmatic suction and this in turn causes contraction of the pelvic floor muscles and deep abdominal muscles (18,19).

The evidence on the effect of hypopressive exercises is scarce, and most of it is focused on their effects on the pelvic floor. Several authors conclude that hypopressive exercises do not provide greater benefit than pelvic floor exercises in terms of function (20,21), increase in cross-sectional area (22), reduction of the hiatus area of the levator ani (23) or pelvic organ prolapse (24).

As for the effect of these exercises on the abdominal wall is still more unknown, but Stüpp et al. (20) observed activation of the transversus abdominis during the performance of a hypopressive exercise measured by surface electromyography. This activation of the transversus abdominis, as indicated above, could have an effect on the interrectal distance.

(10,12,16), therefore we believe that hypopressive exercises could also have an effect on this distance.

So far, to the authors' knowledge, there are only two randomized clinical trials that analyze the effect of exercise programs on inter-straight distance in postpartum women. The first of these is based on pelvic floor muscle training for 16 weeks and found no effect on inter-straight distance (25). More recently, Thabet et al. (26) evaluated the effect of a deep-core stability-strengthening program for 8 weeks and found a decrease in interrectal distance after treatment.

## **2. Study hypothesis**

Performing a program of hypopressive exercises after childbirth results in a greater reduction of the interrectal distance compared to performing a program of classic abdominal exercises.

## **3. Objectives**

- Main objective: To evaluate the effect of two abdominal strengthening programs (classical abdominal exercises *versus* hypopressive abdominal exercises) on the inter-straight distance in postpartum women.
- Secondary objectives: To evaluate possible differences on the effect of programs depending on their obstetric history (maternal age, fetal weight, no. of deliveries, weight gain in pregnancy).

## **4. Type of study**

- Definition of study design: Blinded, parallel group clinical trial.

## **5. Material and methods**

5.1 Field of study: Health and pathology in the postpartum period.

5.2 Definition of study subjects

Study participants will be selected from primary care centers in the Vigo health area.

#### Selection and withdrawal of subjects:

- Inclusion and exclusion criteria. Inclusion criteria were to be between 25 and 40 years of age, to have given birth 8 weeks before beginning the treatment phase of the study and to agree to participate in the study. As exclusion criteria, women with abdominal hernia, pregnancy and abdominal surgeries will be eliminated.
- Withdrawal criteria: participants may voluntarily withdraw from the study at any time. In addition, absence from more than 20% (2 sessions) of the sessions of the exercise program to be carried out in each of the groups will be a criterion for withdrawal.

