#### 5.4 Allocation/randomization procedure

A simple randomization will be performed for each of the groups. Once consent has been obtained, the patients will be randomized to each of the groups according to a list of random numbers previously generated.

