## 5.5 Justification of sample size.

A sample size of 10 participants was established for each group. The estimation of the sample size was based on the study by Sancho et al (10), in which the effect size was between 0.43 and 0.25 of the inter-straight distance for the supraumbilical and infraumbilical measurements. This sample size was calculated using G-Power 3.1 software with an alpha error of 0.05 and a power of 0.95. Considering a loss rate of 30%, a sample size of 14 participants per group was finally estimated.

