#### 5.7 Description of the intervention

From week 8 after delivery, measurements will be taken and the intervention of the two groups will be carried out. First, measurements will be taken, which will be carried out in one day with the procedure explained in the previous point. Afterwards, the participants will carry out the intervention in each of the groups for 6 weeks and then, once these 6 weeks have passed, the final measurements will be taken. None of the abdominal strengthening programs are offered as a regular service to women in the postpartum period in primary care centers.

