##### *Description of the intervention*

*Group 1:* Classic abdominal strengthening exercises (curl-ups, sit-ups and leg-rise), balance exercises, general mobility and upper limb strengthening exercises.

*Group 2:* Hypopressive abdominal exercises, balance exercises, general mobility and upper limb strengthening exercises.

In both groups the exercise programs will have a duration of 6 weeks, with a timing of 2 days per week (1 hour per session), making a total of 12 sessions. The interventions will be carried out in the Navia Health Center, when there is availability of space and prior authorization of the Management of the Health Area of Vigo.

5.8 Timeline and expected completion date. Distribution of tasks among the members of the research team.

The study is expected to begin and end in 2022, provided that health conditions permit and the ethics committee approves. The distribution of tasks of the investigators is as follows:

- [name]: Theoretical development of the project and organization of the rest of the researchers. Randomization of the participants to the treatment groups. Statistical analysis of the data and participation in the writing of the research article derived from this research.
- [name]: In charge of carrying out the exercise program in the classical abdominal strengthening group. Participation in the writing of the article derived from this research.
- [name]: In charge of carrying out the exercise program in the hypopressive abdominal exercises group. Participation in the writing of the article derived from this research.
- [name]: Participation in the theoretical development of the project, in the statistical analysis of the data and in the writing of the article derived from this research. In charge of carrying out the evaluations (pre and post intervention) through ultrasound measurements.
- [name]: Recruitment of participants and collection of obstetric variables.
- [name]: Recruitment of participants and collection of obstetric variables.
- [name]: Recruitment of participants and collection of obstetric variables.
- [name]: Recruitment of participants and collection of obstetric variables.
- [name]: Recruitment of participants and collection of obstetrical variables

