### 5.9 Statistical analysis plan

The dependent variable (DIR) will be analyzed using standard normality tests (Shapiro-Wilk test) to find the normality criteria (29). In the case of a normal distribution of the data, the difference in DIR will be analyzed through an analysis of variance (ANOVA).

The Pearson or Spearman correlation coefficient will be used for the analysis of obstetric variables and their relationship with the DIR.

The main analysis will be based on the difference in DIR pre-post intervention and the comparison between groups by means of a repeated measures analysis. A significance level of  $p < 0.05$  will be established for all variables.

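### Missing too many sessions is a ground for withdrawal and no final scan is provided for these women, so as written the comparison would rest on those who attended enough

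*Protocol*

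**What the plan says.** - **Withdrawal rule.** Under Selection and withdrawal of subjects (protocol section 5.2), "participants may voluntarily withdraw from the study at any time". The same bullet adds a second criterion for withdrawal: "absence from more than 20% (2 sessions) of the sessions of the exercise program". Nothing limits this second criterion to stopping the exercise sessions.
- **Order of events.** Section 5.4: "Once consent has been obtained, the patients will be randomized to each of the groups". The sessions come later, "making a total of 12 sessions" according to the description of the intervention, and section 5.7 places the outcome last: "once these 6 weeks have passed, the final measurements will be taken".
- **Analysis.** Section 5.9: "The main analysis will be based on the difference in DIR pre-post intervention and the comparison between groups". It names no analysis population.
- **Planned loss.** Section 5.5 starts from 10 women per group: "Considering a loss rate of 30%, a sample size of 14 participants per group was finally estimated". It gives no cause for the expected losses.

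The protocol nowhere says whether a woman withdrawn for poor attendance is still scanned at the end of the program.

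**The concern.** Attendance happens after randomization, and the assigned program can influence it through difficulty, discomfort or perceived benefit. The two arms do different abdominal exercises, and section 5.8 assigns a different investigator to lead each, so unequal attendance is plausible.

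The study hypothesis (section 2) is a causal claim that one program reduces the distance more than the other. Randomization supports that claim when women are compared as allocated. If they are removed according to later behavior, a difference between the remaining groups may partly reflect who stayed. A final scan that was never taken cannot be recovered, whatever population a separate SAP defines.

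**Working it through.** **1. Does the rule lead to missing outcomes?** The rule is a criterion for withdrawal, stated beside leaving the study (5.2). It acts after randomization (5.4). The outcome is measured only after 6 weeks (5.7), with no provision for withdrawn women. The main analysis needs that measurement (5.9). Losses are subtracted from the evaluable sample (5.5). Together these imply a comparison among sufficient attenders. The last step is an inference, since no sentence says it outright.

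**2. The plan's own figures.**
- Loss allowance: 14 × (1 − 0.30) = 9.8, about the 10 per group required.
- Attendance threshold: 20% × 12 = 2.4, so more than 20% is first reached at 3 absences (3/12 = 25%). The bracketed 2 sessions is 2/12 = 16.7%, which does not exceed 20%. The percentage and the bracket must be reconciled. The calculation below takes the percentage literally and shows the other reading beside it.

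**3. Share of women the rule would withdraw.** The documents give no attendance data. Assume that each session is missed independently with probability p, so absences X follow Binomial(12, p) and P(X ≥ 3) = 1 − P(0) − P(1) − P(2).

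| Assumed p | 3 or more absences | 2 or more absences |
|---|---|---|
| 5% | 2% | 12% |
| 10% | 11% | 34% |
| 15% | 26% | 56% |
| 20% | 44% | 73% |

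At p = 16%, P(X ≥ 3) = 1 − 0.123 − 0.282 − 0.296 = 0.299. With a threshold of 3, the rule alone therefore exceeds the 30% allowance only above about 16% absence per session. With a threshold of 2, the crossing lies between 5% and 10%.

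**4. Bias.** Let w be an arm's withdrawal rate and g the mean change of its attenders minus that of its withdrawn women. The attenders' mean exceeds the whole arm's mean by w × g. The bias in the group difference is therefore w₁g₁ − w₂g₂, which is (w₁ − w₂) × g when the gap is the same in both arms.
- Assumed low end: 0.10 × 0.5 SD = 0.05 SD.
- Assumed high end: 0.30 × 1 SD = 0.30 SD.
- Equal rates and equal gaps: 0.

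**5. Simulation under no true effect.** Inputs are 14 per arm, assumed withdrawal rates, an assumed correlation of 0.3 to 0.7 between adherence and outcome, and a two-sample t test on the women who remain.
- 30% in both arms: no bias, type I error about 5%.
- 40% versus 20%: bias 0.09 to 0.21 SD, type I error 5.3% to 7.6%.
- 50% versus 10%: bias 0.18 to 0.42 SD, type I error 6.5% to 14.6%.
- With correlation 0, no bias in any of these settings.

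**6. Precision.** The 95% CI half-width for a difference in mean change, in SD units, is t(0.975, 2n − 2) × √(2/n).
- n = 10: 2.101 × 0.447 = 0.94.
- n = 14: 2.056 × 0.378 = 0.78.

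**The case against.** The strongest reply is that the protocol does not declare an analysis of completers. It says that absence is a criterion for withdrawal, not what follows for measurement, and an unseen SAP could name all randomized women as the analysis population. A reader might infer that the protocol forbids a final scan or prescribes a per-protocol analysis. The text does not support that. What it supports is that no final scan is provided for, which an analysis population defined later cannot repair.

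Three further stronger readings are tempting and also fail.
- **That the comparison is shown to be biased, or that randomization is simply lost.** Unequal attendance alone is not enough, and neither is a link between attendance and recovery. Withdrawal must relate to outcome and differ between arms in rate or pattern. The documents show neither. The illustrated 0.05 to 0.30 SD is also well inside the half-width of 0.94 SD, so chance would usually outweigh it in a trial this small. Even so, the confidence interval does not reflect such a bias.
- **That the rule causes much of the expected 30% loss.** Section 5.5 gives no cause. With a threshold of 3 absences, 5% absence per session would withdraw only 2% of women.
- **That changing the rule would narrow the half-width to 0.78 SD.** That is a ceiling. It assumes that every loss comes from the attendance rule and that every such woman returns for her scan, while voluntary withdrawals would continue.

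It is also fair that inviting every randomized woman without qualification would go too far. Consent is signed before delivery, randomization follows consent, and eligibility is checked again after delivery (sections 5.3 and 5.4). Read literally, some randomized women could prove ineligible and have no baseline scan.

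**Conclusion.** The point holds in this form: the protocol withdraws women on a post-randomization event and provides no final scan for them, so as written the main comparison would be made among those who attended enough sessions. That rests on reading sections 5.2, 5.4, 5.5, 5.7 and 5.9 together, with one inferred step.

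The resulting bias is possible and plausible but not demonstrated, and neither its size nor its direction can be derived from the documents. The figures for withdrawal shares, bias and type I error are illustrations under stated assumptions. The case for acting is that the weakness touches the primary comparison, cannot be repaired once the scans are missed, and costs little to remove. The mismatch between the percentage and the bracketed number of sessions is a separate defect in the same sentence.

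**What to change.** 1. In section 5.2, separate missing sessions from leaving the study, and reconcile the 20% with the bracketed 2 sessions.
2. In section 5.7, provide the final ultrasound at the end of the 6 weeks for every randomized woman who was confirmed eligible after delivery and has not withdrawn consent, whatever her attendance.
3. In section 5.9, make the primary analysis by assigned group in all such women, and state how missing final values from voluntary withdrawals are handled.
4. Record the sessions attended, and use the reconciled cut-off only to define a per-protocol sensitivity analysis.

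The cost is a short amendment to these sections and a few more scans by the existing assessor. The primary estimate would then reflect assignment to a program rather than full adherence to it; the sensitivity analysis would still describe the adherent women. The content and schedule of the exercise programs need not change.

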#### 5.3 Recruitment of participants

The study participants will be selected from the following primary care centers in the Vigo health area: Sárdoma, Matamá, Bembrive, Lavadores, Teis, Navia and Coia.

In the pre-delivery consultations, the midwife at each health center will explain to the women the purpose of this study, and they will be invited to participate if they meet the inclusion criteria that can be evaluated before delivery. Patients who meet the criteria must agree to take part in this study by signing the informed consent form. After delivery, it should be checked again whether the women meet the inclusion criteria, for example by the type of delivery, which is something that cannot be known in the consultations during pregnancy.

The midwives from each of the health centers in charge of collecting the participants are:

- [name] (CS Sárdoma, Matamá and Bembrive)
- [name] (CS Navia)
- [name] (CS Coia)
- [name] (C.S Teis)
- [name] (CS. Coia)

#### 5.4 Allocation/randomization procedure

A simple randomization will be performed for each of the groups. Once consent has been obtained, the patients will be randomized to each of the groups according to a list of random numbers previously generated.

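### Simple randomization (section 5.4) does not guarantee the 14 per group planned in section 5.5, and allocation may precede the post-delivery eligibility check: a minor, cheap improvement

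*Protocol*

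**What the plan says.** Section 5.4 gives the method in two sentences. The first is "A simple randomization will be performed for each of the groups". The second says that, after consent, "the patients will be randomized to each of the groups according to a list of random numbers previously generated". No block, stratum or other restriction on group size is mentioned.

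Section 5.5 gives the planned size: "A sample size of 10 participants was established for each group", then "Considering a loss rate of 30%, a sample size of 14 participants per group was finally estimated". That is 28 women in total, with 1:1 allocation implied by the equal group sizes.

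Section 5.3 has midwives invite women at consultations before delivery, with consent signed then. Eligibility is checked again after delivery because some criteria cannot be known earlier. Section 5.7 places the baseline measurements from week 8 after delivery.

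Section 5.8 gives one role "Randomization of the participants to the treatment groups. Statistical analysis of the data", along with project organization. Recruitment, the two exercise programs and the ultrasound measurements are listed under other team members.

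**The concern.** Sections 5.4 and 5.5 do not fit together. The size calculation is expressed as equal groups of 14, but under unrestricted randomization group size is itself random. In a trial of 28 women the arms can differ noticeably by chance. There is also little slack: 30% loss from 14 leaves 14 × 0.7 = 9.8 expected completers, already just under the stated 10.

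The second matter is timing. If a woman is allocated when she consents in pregnancy, she can still be found ineligible after delivery. Such exclusions fall after randomization and can add to any imbalance. Blocking alone would not prevent this, because it balances only the women who are randomized.

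At stake are some precision and the agreement between two sections of the protocol. The validity of the comparison is not threatened by simple randomization as such.

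**Working it through.** **Inputs from the protocol.** 10 evaluable and 14 randomized per group, 30% loss (section 5.5); simple randomization (section 5.4); effect size 0.25 to 0.43, alpha 0.05, power 0.95 (section 5.5); a repeated-measures comparison of two groups before and after (section 5.9).

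**Assumptions, not in the protocol.** The effect size is Cohen's f, taken at 0.43, and the pre-post correlation rho is 0.5. The split probabilities in step 2 need neither.

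**1. The plan's own figure.** For the group-by-time interaction with m = 2 time points, the noncentrality is λ = f² × N × m/(1 − rho). With N = 20, λ = 0.1849 × 20 × 4 = 14.79. On 1 and 18 degrees of freedom this gives power 0.953, so the stated 10 per group is reproduced. For loss, 10/0.7 = 14.29. Rounding up would give 15, but the stated 14 is close enough to take as it stands.

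**2. How often 28 women split evenly.** The size of one arm is Binomial(28, 0.5). P(14:14) = C(28,14)/2²⁸ = 40,116,600/268,435,456 = 14.9%. The other probabilities are two-sided tail sums. The expected difference between the arms is 4.2 women.

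**3. What imbalance costs.** Efficiency relative to equal arms is 4·n₁·n₂/N². At 10:18 this is 720/784 = 0.918; on average it is 1 − 1/28 = 0.964. For power, apply 30% loss to each arm and use λ = d²·n₁n₂/(n₁+n₂), with d = 2f·√(m/(1 − rho)) = 0.86 × 2 = 1.72, so d² = 2.958. At 14:14 (9.8 and 9.8 completers), λ = 2.958 × 4.9 = 14.50. At 10:18 (7.0 and 12.6), λ = 2.958 × 4.5 = 13.31.

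| Split of 28 | P(this split or worse) | Completers after 30% loss | Power |
|---|---|---|---|
| 14:14 | – | 9.8 and 9.8 | 94.9% |
| 12:16 | 57.2% | 8.4 and 11.2 | 94.5% |
| 11:17 | 34.5% | 7.7 and 11.9 | 93.9% |
| 10:18 | 18.5% | 7.0 and 12.6 | 93.1% |
| 9:19 | 8.7% | 6.3 and 13.3 | 91.9% |
| Average over all splits | – | – | 94.1% |

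The average loss is 94.9 − 94.1 = 0.8 points; at 10:18 it is 94.9 − 93.1 = 1.8 points.

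**4. Range over the assumptions.** The same formula with f of 0.25, 0.34 or 0.43 and rho of 0.5, 0.7 or 0.8 gives an average loss between almost 0 and 1.6 points, and a loss at 10:18 of at most about 3.6 points. For example, at f = 0.25 and rho = 0.5, power is 55.3% at 14:14, 53.7% on average and 51.8% at 10:18. The low level of power there comes from the smaller effect and is a separate matter. The loss from imbalance stays small throughout.

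**5. After the fix.** With blocks of 4 and 6 every complete block is balanced and has even length. Because 28 is even, a block cut off at the 28th woman contributes 2 or 4 women. Whichever way it is cut, the arms differ by at most 2, so the final split is 14:14 or 13:15. Efficiency at 13:15 is 4 × 13 × 15/784 = 0.995.

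**The case against.** Simple randomization is unbiased and the least predictable scheme, and the planned comparison does not need equal arms. The 14 per group can be read as a recruitment target, not a promise about the split; the plan says "a sample size of 14 participants per group was finally estimated". The wording of section 5.4 is loose enough that a list for two groups of set size cannot be ruled out, though unrestricted allocation is the likelier reading. All of this stands, and it is why the point is minor.

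Three stronger readings are tempting but unsupported.

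- **An open list.** A reader might infer from a pre-generated list, held by the role that organizes the project, that upcoming assignments are known and could steer enrolment. The protocol does not say that the list is open or who can see it. Section 5.8 lists randomization separately from recruiting, teaching and measuring, and sections 5.6 and 9 keep the assessor blinded. The protocol describes no concealment mechanism, but that is silence, not a stated error.
- **An arm below 10 breaks the size calculation.** Precision depends on both arms, through their harmonic mean. At 9:19 that is 2 × 9 × 19/28 = 12.2 before loss, above 10.
- **Blocking is free.** Instructors know their own program, so small fixed blocks could reveal later assignments. Varying, undisclosed sizes limit this without removing it.

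**Conclusion.** The point holds as a minor one. Simple randomization of 28 women does not guarantee 14 per group: the exact split occurs in about 15% of trials and 10:18 or worse in about 18%. These figures rest only on 28 women and 1:1 allocation. The cost in power is about 1 point on average and about 2 points at 10:18, under the assumed f = 0.43 and rho = 0.5; over the wider range examined it reaches 1.6 points on average and about 3.6 points at 10:18. The method remains valid.

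The timing issue follows from reading sections 5.3 and 5.4 together: as written, allocation can precede the post-delivery eligibility check. How many women would be excluded at that check is not given, so the added imbalance cannot be quantified.

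**What to change.** Amend section 5.4 in two respects.

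1. Replace simple randomization with 1:1 permuted blocks of randomly varying size (for example 4 and 6), with the sizes not disclosed to those who recruit, teach or measure.
2. State that each assignment is released from a concealed list, for example in sequentially numbered opaque envelopes, only after eligibility has been confirmed following delivery and the baseline ultrasound recorded.

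The cost is a few sentences and a new list before enrolment, with no extra participants or visits. The drawbacks are slight predictability at block ends, limited by the varying sizes and the concealment, and a possible final split of 13:15. Losses after allocation can still make the completers unequal.

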## 5.6 Primary and secondary variables

The difference in inter-straight distance (DIR) before and after the intervention will be used as the treatment effect variable. The researcher who will carry out the measurements will be blinded and will not know to which group each participant belongs. The measurements will be carried out at the Navia Health Center, when space is available and with prior authorization from the Management of the Vigo Health Area.

- Measurement of DIR: Participants will be positioned in the supine position with knees bent at 90° with feet resting on the table and arms alongside the body. After being instructed to perform an abdominal crunch, subjects are asked to separate the head and elevate the shoulders until the scapula detaches from the table.

Ultrasound images will be recorded with an ultrasound scanner (GE Logic-e; 4-12 MHz, 39 mm linear transducer; B-mode), in a supine resting position and a muscle activation position (isometric contraction), 2 cm and 5 cm above the umbilicus.

To ensure that the two DIR measurements (2 cm and 5 cm above the umbilicus) are taken at the same location, the skin is marked with a water-soluble pen.

Ultrasound image collection will be performed immediately at the end of exhalation, as determined by visual inspection of the abdomen following the recommendations of Teyhen et al. (27) Special attention will be paid to the pressure exerted on the ultrasound probe on the patient to avoid reflexive response of the abdominal musculature (28).

For ultrasound image acquisition, the lower edge of the transducer will be placed over the mark made and moved laterally until the medial edges of both anterior rectus muscles can be visualized. The orientation of the transducer will be adjusted to

optimize image visualization. The collected ultrasound images will be exported to DICOM format for further measurement, analyzed by the same investigator, using a customized Matlab code (Image Processing Toolbox, Mathworks Matlab, USA) following the procedures described by Mota et al. (28). There is a good intra-evaluator reliability in DIR ultrasound images, with confidence interval values higher than 0.90(27).

These will be collected as independent variables:

- Group to which the patient is randomized (hypopressive abdominal exercises group and classic abdominal exercises group).

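### As written, consent alone triggers randomization, so allocation can precede the post-delivery eligibility check and the baseline ultrasound

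*Protocol*

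**What the plan says.** Section 5.3 has the midwife explain the study at pre-delivery consultations. Women are invited on a partial check: "they will be invited to participate if they meet the inclusion criteria that can be evaluated before delivery". The next sentence deals with consent: "Patients who meet the criteria must agree to take part in this study by signing the informed consent form". The section then provides for a second check: "After delivery, it should be checked again whether the women meet the inclusion criteria, for example by the type of delivery". Its stated reason is that some facts cannot be known during pregnancy.

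Section 5.4 fixes when allocation happens: "Once consent has been obtained, the patients will be randomized to each of the groups". It names no other condition and gives no date.

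Section 5.7 starts the study procedures later: "From week 8 after delivery, measurements will be taken and the intervention of the two groups will be carried out". The first ultrasound is taken then, before the 6-week program. Section 5.6 builds the outcome on that scan: "The difference in inter-straight distance (DIR) before and after the intervention will be used as the treatment effect variable".

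Under the selection criteria in section 5.2, inclusion requires that a woman gave birth 8 weeks before treatment begins, and "women with abdominal hernia, pregnancy and abdominal surgeries will be eliminated".

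On blinding, sections 5.6 and 9 keep the measuring researcher unaware of the group during measurement and data entry. Neither section mentions the women, the midwives or whoever repeats the eligibility check.

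**The concern.** A randomized comparison is best protected when eligibility is settled and baseline recorded before anyone is assigned. If allocation comes at antenatal consent, two things follow.

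- The protocol plans a re-check because it expects that some women may fail it. Those exclusions would fall on women who already have an arm. If whoever judges eligibility knows the arm, or if women decide whether to continue because of it, the groups that reach week 8 are no longer simply the groups that were randomized. With 28 women planned, a few such losses matter.
- The outcome is a change from a baseline read at least 8 weeks after allocation. A woman who knew her arm could change her activity, or drop out, before that baseline exists. An analysis plan cannot afterwards supply a baseline taken before randomization.

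**Working it through.** **Order of steps.** Setting the sections side by side gives this sequence:

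1. Invitation at antenatal visits, on the criteria assessable then (5.3).
2. Consent, described between the invitation and the post-delivery check (5.3).
3. Randomization, triggered by consent (5.4).
4. Delivery, then the eligibility re-check (5.3).
5. Baseline ultrasound from week 8 postpartum (5.7).
6. Six-week program, then the final ultrasound (5.7).

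No section makes step 3 wait for step 4 or 5. At an antenatal step 3 a woman has not yet given birth and is still pregnant, so the criteria in 5.2 cannot yet be confirmed for her.

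**Reproducing the planned size.** Inputs from section 5.5: effect size 0.43 (upper end of the cited range), alpha 0.05, power 0.95, 10 per group, 30% loss, 14 per group. Two inputs are assumptions because the protocol does not give them: that 0.43 is Cohen's f, and that the pre-post correlation ρ is 0.5. For the group-by-time interaction with 2 groups and m = 2 time points:

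- λ = N × f² × m / (1 − ρ) = 20 × 0.1849 × 2 / 0.5 = 14.79, with 1 and 18 degrees of freedom.
- Power from the noncentral F distribution is 0.953, which matches 10 per group.
- Allowing for loss, 28 × 0.7 = 19.6 women, with power 0.949.

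The match holds only at f = 0.43. At the lower cited value, 0.25, the same calculation needs 54 women in total. That is a separate matter.

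**If pre-start losses come on top of the 30%.** Let e be the share of randomized women excluded or lost before the program starts. The protocol gives no figure, so a range of 10–30% is assumed. Analyzable women = 28 × (1 − e) × 0.7.

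| e | Analyzable women | Per arm | λ = 0.7396 × N | Power at f = 0.43 |
|---|---|---|---|---|
| 0 | 19.6 | 9.8 | 14.50 | 0.949 |
| 10% | 17.6 | 8.8 | 13.05 | 0.923 |
| 20% | 15.7 | 7.8 | 11.60 | 0.885 |
| 30% | 13.7 | 6.9 | 10.15 | 0.831 |

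To keep 20 analyzable women, 20 / 0.7 / (1 − e) would have to be randomized: about 32, 36 and 41 for e = 10%, 20% and 30%.

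**If the 30% already covers them.** The e = 0 row applies as long as total loss stays within 30%, and there is no further cost in power.

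**The case against.** The strongest reply is that the timing is inferred. The sentence on signing consent carries no date, and at least one inclusion criterion cannot be met before birth. The wording in 5.4 may set only a minimum condition, with allocation made later. This stands as a caution: the document does not prove that women will be randomized during pregnancy. But antenatal signing is the natural reading, nothing delays allocation beyond it, and staff following the text could randomize then.

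The second reply is that no bias is shown.

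- No section says that women or midwives learn the arm at allocation.
- Section 5.8 gives randomization to one investigator and recruitment to others.
- Section 9 has the group column filled in only at the end of the study.
- Type of delivery, the protocol's own example of a late exclusion, should not depend on assignment to a postpartum program. If those checking are unaware of the arm, such exclusions cost numbers without tilting the comparison.
- Section 5.7 says neither program is a regular primary-care service, which limits early access there.
- The assessor is blinded, so the reading itself is protected.

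All of this stands and narrows the point. What it does not supply is a statement that the women and those re-checking eligibility are unaware of the arm.

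The third reply concerns numbers. Section 5.5 gives a 30% loss rate without limiting it to the exercise period, so losses before the start may already be allowed for. This also stands, and it makes the table above conditional.

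**Conclusion.** The point holds as a fault in the written order. Read literally, sections 5.3, 5.4 and 5.7 allocate women before eligibility can be confirmed, allow exclusions after allocation, and take the baseline of the pre-post outcome after allocation.

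Three stronger readings are tempting, and the protocol supports none of them.

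- A reader might infer that women will be told their arm and will exercise or decline because of it. Disclosure before baseline is nowhere stated, so this is a risk left open and not a demonstrated bias.
- A reader might infer that the baseline measurement is itself biased. The assessor's blinding argues against that; the exposure is to selection and to behaviour before the scan.
- A reader might infer that the trial will shrink to 7–9 women per arm. That requires both an assumed 10–30% pre-start loss and a 30% allowance that excludes it, and the protocol settles neither. Under both conditions about 18 to 14 women remain and power is about 0.92 to 0.83 instead of 0.95, taking f = 0.43 as Cohen's f with a correlation of 0.5. If the 30% covers all loss after allocation, the fall in power disappears and only the sequencing problem remains.

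**What to change.** Change section 5.4 to state that consent may be obtained antenatally, but that randomization takes place only after eligibility has been re-confirmed following delivery and the baseline ultrasound has been recorded, immediately before the program starts. Count the 14 per group from that point. Women who fail the re-check are then never allocated, and the 30% allowance has a clear starting point.

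No extra visit, measurement or staff is needed. The change does not save the women lost before week 8. They must still be replaced, so the midwives would have to consent more women antenatally to reach 28 eligible women at randomization. On the assumed 10–30% pre-start loss, that is about 28 / 0.9 = 31.1 to 28 / 0.7 = 40, or 32 to 40 consents. The change should be made before the first woman is randomized, since a pre-allocation baseline cannot be recovered later.
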